### 2.5. Measurement Instruments

All quantitative outcome measures are validated for Greek adult populations and administered at baseline (T0) and post-intervention (T2). Qualitative data collection occurs at mid-intervention (T1, Week 8) and post-intervention (T2, Week 12).

The quantitative measurement instruments are presented in the following Table 1.

The qualitative data collection instruments will be the following (Supplementary File S3 [27]):

Phenomenological Interview Guide. A semi-structured interview protocol guides qualitative data collection at mid-intervention (T1, Week 8, *n*~30) and post-intervention (T2, Week 12, *n*~30). The interview guide contains open-ended questions focused on: (1) embodied experience and somatic awareness (e.g., “Can you describe moments when you felt particularly aware of your body during the sessions?” and “How did your relationship with your breath or bodily sensations evolve across the weeks?”); (2) emotional awareness and regulation (e.g., “What emotional experiences stood out for you during the program?”); (3) movement identity and creative expression (e.g., “How has your relationship with dance or your own movement changed?”); (4) meaning-making and personal insights (e.g., “What meaning did you make from your experiences in the program?” and “Were there moments that connected with your personal life, values, or self-understanding?”); (5) perceived changes like psychological, physical, and social (e.g., “Since the beginning of the program, what changes, if any, have you noticed in yourself?” and “Do you feel different in daily life because of this experience?”); and (6) program structure and safety (e.g., “How did you experience the environment and safety of the sessions?”). Interviews are digitally recorded (after participant consent) and transcribed verbatim for qualitative analysis.

Weekly Journaling Prompts. Participants provide weekly written reflections using standardized prompts distributed at the end of each session (5–10 min per entry). Prompts guide attention to: (1) breath and embodiment (e.g., “Which movements or exercises helped you feel embodied or aware of your internal sensations?”); (2) emotional states and internal reactions (e.g., “Did you notice any shifts in mood, tension, or energy throughout the session?”); (3) awareness of movement and creative exploration (e.g., “Were there moments where movement felt effortless, challenging, playful, or meaningful?”); (4) meaning-making (e.g., “How did today’s experience connect with your life outside the studio?”); and (5) change across sessions (e.g., “Compared to earlier weeks, do you notice any changes in your awareness, emotions, or movement?”). Journals are completed on standardized paper forms, collected weekly, and analyzed for thematic patterns regarding embodied experience, affective change, and perceived transformation.

### 2.6. Intervention and Control Conditions

The intervention group will consist of participants who attend 12 weekly sessions (90–100 min each) structured across three phases: (1) Foundations (Weeks 1–4), (2) Embodied Exploration (Weeks 5–8), and (3) Expressive Integration (Weeks 9–12). Each session integrates eight standardized components (warm-up/breath grounding, technical dance work, conditioning, mindful break, rhythm/improvisation, choreographed sequences, cool-down/reflective integration, phenomenological journaling). Detailed component descriptions, facilitator language, and session structure are specified in Supplementary File S1 [27].

The control group will consist of participants who continue usual recreational dance activities (preferred modern dance and/or contemporary classes) for 12 weeks, excluding mind–body practices (e.g., yoga, Pilates, tai-chi) that share overlap with the intervention. Control participants do not receive mindfulness training, somatic cuing, or reflective journaling prompts. After post-intervention assessment (T2, Week 12), control participants are offered access to the full 12–week Dance-Mindfulness program at no cost (delayed intervention, ethical equity control).

### 2.7. Data Collection and Analysis

Self-report questionnaires (SWLS, DASS-21, MAAS, SHS, LIS) are administered on paper at baseline (T0) and post-intervention (T2) by trained site coordinators in quiet studio environments (~20–30 min per assessment). Questionnaires are entered into a secure electronic database with double-entry verification.

Demographic and baseline characteristics are summarized using descriptive statistics (means, standard deviations, medians, frequencies, percentages). Shapiro–Wilk tests and visual inspection (Q-Q plots, histograms) assess normality for all primary outcome variables. Between-group demographic comparisons use independent-samples *t*-tests (continuous) and chi-square tests (categorical). Internal consistency is assessed using Cronbach’s alpha (α ≥ 0.70); test–retest reliability via intraclass correlation coefficients (ICC ≥ 0.70) in the control group.

If normality is met (Shapiro–Wilk *p* > 0.05), a 2 (Group) × 2 (Time) mixed-model repeated-measures ANOVA is conducted on each primary outcome, with Bonferroni-corrected α = 0.01 to control Type I error. Alternative testing via MANOVA (Wilks’ Lambda, α = 0.05) proceeds to univariate ANOVAs if significant. ANCOVA with T0 baseline covariates is conducted with Levene’s test assessing homogeneity of variance; if violated (*p* < 0.05). Effect sizes and 95% confidence intervals are reported.

If normality is violated (Shapiro–Wilk *p* < 0.05), non-parametric tests will be used: Friedman’s test (within-group time effects), Mann–Whitney U (between-group comparisons), Wilcoxon signed-rank test (within-group pre–post). Post hoc pairwise comparisons use Bonferroni-corrected alpha. Pearson correlations (Bonferroni-corrected) for normally distributed variables; Spearman’s rank-order correlations for non-normal variables. Correlations ≥ |0.30| are highlighted. Quantitative analyses use IBM SPSS v. 28; results are reported per CONSORT guidelines [31] with summary statistics, 95% confidence intervals, and effect sizes. Significance level: α = 0.05 (two-tailed) unless otherwise specified (Bonferroni-corrected α = 0.01).

In qualitative analysis, semi-structured interviews (*n*~30, T1 Week 8 and T2 Week 12; maximum variation sampling) and weekly journal entries are collected from intervention participants. Interview data are analyzed using Interpretative Phenomenological Analysis (IPA; six-step procedure per [23,40,41] with inter-rater reliability assessed via Cohen’s kappa (κ ≥ 0.70). Weekly journals are analyzed using Reflexive Thematic Analysis [42,43] with phase-specific coding (Weeks 1–4, 5–8, 9–12). Two independent coders conduct all qualitative analysis; discrepancies are resolved through consensus. Analysis examines themes related to embodied awareness, emotional regulation, nervous system resilience, relational presence, and personal transformation (detailed methodology in Supplementary File S3 [27]).

Quantitative measures (both groups, T0–T2) test intervention efficacy; qualitative data (intervention group only) explores embodied mechanisms of change, providing mechanistic understanding complementary to quantitative hypothesis testing.

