### 2.2. Study Setting

The study will be conducted across private dance schools in Thessaly, Greece. All baseline (T0) and post-intervention (T2) quantitative assessments will be held in quiet, standardized studio environments at each participating dance school to ensure ecological validity and participant accessibility. All qualitative interviews (T1 Week 8, T2 Week 12) will be conducted in private, quiet locations at the respective dance schools. The 12-week dance-mindfulness intervention will be delivered at the designated dance studios in Thessaly region in Greece. Each studio meets the standardized environmental specifications to ensure consistent and safe delivery across sites (Supplementary File S2 [27]).

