### 2.4. Sample Size and Recruitment

To determine the appropriate sample size for this study, a power analysis was conducted using GPower 3.1 software [32]. The analysis was based on a repeated-measures design with two groups (experimental and control), with measurements taken at baseline and post-intervention. The following parameters were used: Effect Size (Cohen’s d) = 0.50 (medium effect); Alpha Level (α) = 0.05 (5% significance threshold); Power (1 − β) = 0.80 (80% probability of detecting a true effect); two measurement time points (pre- and post-intervention); and two groups (experimental and control). According to the power analysis, the minimum sample size required to achieve sufficient statistical power is 114 participants, with 38 participants in the control group and 76 in the experimental group.

Participants will be informed about the study through targeted outreach at private recreational dance schools in four cities (Larissa, Trikala, Karditsa, Kalampaka) within the Thessaly region, Greece, with an estimated 1–2 participating schools across these cities. Recruitment methods include flyers, posters, verbal announcements during dance classes, and direct recruitment by dance school directors. Recruitment occurs over an anticipated 1–2 month period, with baseline assessments completed by the end of Month 2. During initial contact, prospective participants receive a participant information sheet detailing study aims, procedures, risks, benefits, confidentiality protections, and withdrawal rights. The information sheet describes the study as “a 12-week integrated modern dance program” without mentioning mindfulness components, to minimize selection bias toward mindfulness-seeking participants. Individuals expressing interest undergo preliminary telephone or in-person screening with a trained site coordinator to assess adherence to inclusion and exclusion criteria (Section 2.3). Those meeting preliminary eligibility criteria are informed of the next steps. Individuals with intense mental health distress or active engagement in concurrent mindfulness-based interventions are offered future participation following symptom resolution or completion of conflicting interventions, rather than immediate exclusion.

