Content & Recovery Work	Foundational settling: gentle supine or seated positioning with interoceptive grounding, participants notice body weight settling into floor/chair, breath becoming audible and steady. Facilitator guides attention to: “Feel where your body contacts the surface beneath you… feel your weight releasing… feel your breath becoming calm and easy” [17]. No additional movement; stillness prioritized. Movement structured around parasympathetic anchoring rather than cognitive narrative. Develops embodied confidence: “My nervous system can settle. I am safe. Recovery is natural.”	Intermediate settling: seated or supine with gentle proprioceptive grounding. Facilitator emphasizes oscillation: “Notice: your heartbeat is slowing. Your breathing is deeper. Your nervous system is finding its way back to calm”. Participants practice HRV-aware settling, tracking visible signs of vagal reactivation (slowed heart rate, deeper breathing, muscle relaxation). Acknowledgment of recovery process: “This is your parasympathetic nervous system reactivating. This is your body’s natural return to safety.” Nervous system learns: oscillation is reliable; recovery is predictable.	Advanced settling: supine with collective presence. Facilitator emphasizes relational co-regulation: “You are settling. Notice others around you also settling. We are together in this calm. Feel that you belong in this shared safety”. Participants experience “feeling felt” through group nervous system coherence, a phenomenon where one person’s regulated state influences others’ autonomic nervous systems [10,17]. Recovery metric shifts from individual interoception to relational attunement. “Sense of self” (SPA: sensation, perspective, agency) integrates with “sense of we” through co-regulated presence.

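### Intervention participants are taught in shared classes, but no planned test allows for within-class correlation; any positive ICC pushes the error rate above the stated 0.01

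*Protocol article*

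**What the plan says.** Allocation is by individual, 2:1 (Sections 2.1 and 2.4), giving 76 intervention and 38 control participants. Trained facilitators then deliver the intervention in weekly sessions (Section 3.1). The work is collective: partner, small-group and ensemble choreography (Section 3.3, Component 6; Table 7), and settling exercises that rely on the group regulating itself together (Component 4). Table 5 states the mechanism outright: "one person’s regulated state influences others’ autonomic nervous systems".

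For the analysis, Section 2.7 specifies that "a 2 (Group) × 2 (Time) mixed-model repeated-measures ANOVA is conducted on each primary outcome", "with Bonferroni-corrected α = 0.01 to control Type I error". It adds a MANOVA route, an ANCOVA with baseline covariates, and Friedman, Mann–Whitney and Wilcoxon tests if normality fails. None has a class or facilitator term. The term mixed-model here describes a between-subject factor crossed with a within-subject factor; no random class effect is mentioned.

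Section 2.4 bases the sample size on d = 0.50, "Alpha Level (α) = 0.05 (5% significance threshold") and "Power (1 − β) = 0.80 (80% probability of detecting a true effect"), with no ICC or design effect. The number and size of classes are not given. On sites, Section 2.2 says "The study will be conducted across private dance schools in Thessaly, Greece", and Section 2.4 describes outreach in four cities "within the Thessaly region, Greece, with an estimated 1–2 participating schools across these cities".

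**The concern.** People who share a class also share a facilitator, a room, a timetable and each other. Where that moves their scores in the same direction, 76 participants carry less information than 76 independent ones. A test that ignores this reports intervals that are too narrow and p-values that are too small. The problem arises during treatment, so individual randomization does not remove it.

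Two things make it more than a formality here. The protocol's own theory predicts that class members influence one another, so independence within a class sits awkwardly with the rationale. And the 0.01 level was chosen expressly to control Type I error. A result driven by one or two strong classes, or by one effective facilitator, could be reported as an effect of the programme.

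**Working it through.** **Inputs from the protocol.** 76 intervention and 38 control participants, d = 0.50, α = 0.05 and power 0.80 in the sample-size calculation (Section 2.4); two-sided testing at 0.01 per primary outcome (Section 2.7).

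**Assumptions, because the protocol is silent.** Number of intervention classes k, hence class size m = 76/k; ICC of the analysed quantity (change, or T2 adjusted for T0); equal total variance in both arms; controls independent.

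**Step 1: reproduce 114.** For two independent means at 2:1, the control-arm size is (z_α + z_β)² × (1 + 1/2) / d².
- One-sided 0.05: (1.645 + 0.842)² × 1.5 / 0.25 = 37.1, so 38 control and 76 intervention, total 114. The exact t calculation gives the same.
- Two-sided 0.05: 48 + 96 = 144.
- The repeated-measures F variants tried gave totals from 11 to 97.

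So 114 is matched by a calculation with independent participants and a design effect of 1.

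**Step 2: variance of the arm difference.** The design effect in the intervention arm is DEFF = 1 + (m − 1) × ICC. True variance divided by assumed variance is

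R = (DEFF/76 + 1/38) / (1/76 + 1/38) = (DEFF + 2) / 3.

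**Step 3: actual error rate at nominal two-sided 0.01.** This is 2 × [1 − Φ(2.576/√R)]. Example with 4 classes (m = 19) and ICC 0.05: DEFF = 1 + 18 × 0.05 = 1.90; R = 3.90/3 = 1.30; 2.576/1.140 = 2.259; rate 0.024.

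| ICC | 6 classes (m = 12.7) | 5 classes (m = 15.2) | 4 classes (m = 19) | 2 classes (m = 38) |
|---|---|---|---|---|
| 0 | 0.010 | 0.010 | 0.010 | 0.010 |
| 0.01 | 0.012 | 0.012 | 0.012 | 0.015 |
| 0.02 | 0.013 | 0.014 | 0.015 | 0.021 |
| 0.05 | 0.018 | 0.021 | 0.024 | 0.043 |
| 0.10 | 0.029 | 0.034 | 0.042 | 0.085 |

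With classes of 10 and ICC 0.01 the rate is 0.011.

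**Step 4: check by simulation.** With 40,000 runs per setting, ICC 0.05 gave 0.0195 for 5 classes of 15, 0.0236 for 4 classes of 19 and 0.0427 for 2 classes of 38. Mann–Whitney with 5 classes of 15 at ICC 0.05 gave 0.018, so the rank-test fallback does not avoid the problem.

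**Step 5: clustered controls.** If controls were clustered to the same degree, R would equal DEFF. At m = 15 and ICC 0.05, R = 1.70 and the rate is 0.048. This is an upper illustration, because the protocol does not say how many controls share a class.

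**Step 6: power at N = 114.** Power is Φ(0.5/SE − z), with SE = √(DEFF/76 + 1/38). At m = 15:

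| ICC | One-sided 0.05 (the basis that reproduces 114) | Two-sided 0.01 (the planned test) |
|---|---|---|
| 0 | 0.81 | 0.48 |
| 0.01 | 0.79 | 0.45 |
| 0.05 | 0.73 | 0.38 |
| 0.10 | 0.67 | 0.31 |

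The gap between the two columns at ICC 0 is a separate matter of which α the calculation used. Clustering accounts only for the fall down each column.

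**The case against.** The strongest reply is that the protocol contains no ICC, class count or class size, so the damage is unknown. That stands: at ICC 0 there is none, and at ICC 0.01 with small classes it is negligible. Autonomic co-regulation in a settling exercise makes correlation plausible, but it does not show how large the correlation will be on self-report scales of life satisfaction, happiness, mindfulness, distress or leisure involvement. The intervention manual, the 12 h training, observed mock teaching, audio fidelity checks and supervision should reduce facilitator differences, though they cannot exclude them. Make-up sessions may blur class membership.

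Three stronger readings are tempting, and the documents do not support them.
- **That the 0.01 rate is certainly exceeded.** It is exceeded only if the ICC is above zero.
- **That leaving out a school term also inflates the error rate.** With individual randomization, school differences common to both arms add noise to both. A 20,000-run simulation with four schools carrying 10% of the variance, and school ignored, gave 0.0105 at nominal 0.01.
- **That one to two schools over four cities is an error.** It may mean per city, or outreach in four cities that yields one or two schools in all. It is unclear, not demonstrably wrong.

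It is also fair to say that a random class effect is poorly estimated with 4 to 6 classes, and that with fewer it can hardly be distinguished from treatment. That limits what any analysis can deliver; the independence tests conceal the limit and do not escape it.

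**Conclusion.** The concern holds in conditional form. The omission and its direction follow from the document: the tests are written out, none allows for classes, and 114 is matched by a calculation for independent participants. An analysis plan that added a class effect would have to depart from Section 2.7, so this is not merely detail left for later.

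The size rests on assumed inputs. With 4 to 6 intervention classes and independent controls, the nominal 0.01 becomes about 0.013–0.015 at ICC 0.02, 0.018–0.024 at ICC 0.05 and 0.029–0.042 at ICC 0.10. It is near 0.04 at ICC 0.05 if there are only two classes, and close to 0.01 at ICC 0.01 with small classes. Controls who share classes could add to this; whether they do is not stated.

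**What to change.** 1. Keep a class and a facilitator identifier for every intervention participant. Attendance is already recorded at each session, so these should be recoverable. Record the same for controls who share a class, where possible.
2. Make the between-group analysis T2 = arm + T0, with a random class intercept in the intervention arm only (a partially nested model) and Satterthwaite or Kenward–Roger degrees of freedom.
3. Restate the power of N = 114 for a stated range of ICCs and class sizes, at the α of the planned test.
4. Say whether the one to two schools are per city or in total, since this governs the number of classes.
5. If there turn out to be very few classes, declare that class or facilitator effects cannot be fully separated from the programme effect.

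The cost is one or two recorded variables and a different model, both possible until analysis starts. The price is wider intervals and few degrees of freedom. A school term, or stratifying the randomization by school if it has not yet taken place, is an optional gain in precision and does not correct the error rate.

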### 1.2. Aim and Objectives

The aim of this study is to develop and theoretically justify a comprehensive, 12-week integrated dance-mindfulness protocol grounded in polyvagal theory, motor learning science, and embodied phenomenology. The protocol systematically operationalizes the cultivation of nervous system resilience, technical dance competence, authentic creative expression, and social belonging within structured modern dance theater (Imperial Society of Teachers of Dancing-ISTD syllabus [26]) for community-based adult dancers. The study investigates whether this integrated protocol produces measurable psychological improvements compared to standard dance instruction, and whether participants report enhanced embodied meaning-making and somatic awareness through phenomenological accounts. The specific objectives are:(1)To develop and operationalize a comprehensive, 12-week integrated dance-mindfulness protocol grounded in neuroscience, motor learning, and embodied phenomenology that systematically integrates theory with practice.(2)To evaluate the protocol’s effectiveness using a mixed-methods RCT design comparing intervention and control groups on quantitative and qualitative outcomes.(3)To evaluate the intervention’s effectiveness on psychological well-being and embodied experience.

Based on the theoretical framework and structure of the 12-week intervention, it is hypothesized that participants in the dance mindfulness intervention group will demonstrate significantly greater improvements than those in the control group across primary quantitative outcomes (life satisfaction, subjective happiness, psychological distress, mindful attentional capacity, and leisure involvement) and secondary qualitative outcomes (enhanced somatic awareness, nervous system resilience, technical confidence, creative expression, relational belonging, social connection and embodied meaning-making).

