## 4. Expected Results

Based on the integrated theoretical framework (polyvagal theory, motor learning science, embodied phenomenology) and the structured 12–week protocol design, the following outcomes are expected:

Quantitative outcomes. Intervention participants are expected to demonstrate significantly greater improvements from baseline to post-intervention compared with controls on primary outcome measures: increased life satisfaction and subjective happiness, decreased psychological distress, and enhanced mindful attentional capacity and leisure involvement. These improvements are hypothesized to reflect the intervention’s integration of nervous system regulation (breath-movement synchronization), embodied awareness practices, and relational belonging within the dance context.

Qualitative outcomes. Phenomenological analysis of interview and journal data is expected to reveal a progressive developmental arc across the three intervention phases. Early-phase reflections are anticipated to center on foundational somatic awareness and nervous system regulation; mid-phase reflections to incorporate relational presence and emotional attunement; and late-phase reflections to synthesize embodied learning, relational connection, and authentic expression into coherent narratives of transformation. Control group reflections are expected to remain focused on conventional dance engagement (technique, enjoyment) without the developmental trajectory or transformational narratives anticipated in the intervention group. Individual variability in response will be examined descriptively to identify participant and contextual factors influencing intervention responsiveness.

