## 6. Conclusions

This protocol outlines a comprehensive, evidence-informed 12-week integrated dance-mindfulness intervention designed to systematically operationalize polyvagal theory, motor learning science, somatic education, and embodied phenomenology into coherent pedagogical practice. Grounded in principles of progressive nervous system development, technical skill optimization, and relational attunement, the proposed three-phase framework addresses a critical gap in recreational dance education by bridging abstract neuroscientific theory and concrete teaching methodology. The intervention responds to what recreational dancers authentically seek: nervous system resilience, embodied confidence, authentic creative expression, and social belonging—motivations that are largely absent from both clinical and elite professional dance research.

If supported by future data, this approach may offer a replicable and adaptable model for transforming recreational dance from technical skill development alone toward a comprehensive well-being practice grounded in contemporary neuroscience and embodied meaning-making. Beyond recreational dance, findings will inform contemplative movement education broadly (yoga, tai-chi, Pilates, qigong) and clarify scalability across educational, community, and clinical settings, with implications for integrating neuroscience-informed embodied practice into diverse organizational contexts. This protocol contributes to evidence-based pedagogical innovation by demonstrating that systematic integration of nervous system regulation, motor learning, somatic reflection, and relational engagement produces superior psychological and embodied outcomes compared to traditional dance instruction alone, fundamentally advancing how movement education serves adult psychological well-being and authentic self-expression.

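### Flat Bonferroni at 0.01 on five unranked primary outcomes is valid, but Holm's step-down procedure holds the same family-wise rate and never rejects less

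*Protocol article*

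**What the plan says.** Section 1.2 states the hypothesis that intervention participants "will demonstrate significantly greater improvements than those in the control group across primary quantitative outcomes" and lists five: life satisfaction, subjective happiness, psychological distress, mindful attention and leisure involvement. Section 4 repeats the expectation as "significantly greater improvements from baseline to post-intervention compared with controls on primary outcome measures", with a direction for each. No outcome is ranked above the others.

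Section 2.7 matches these to five questionnaires (SWLS, DASS-21, MAAS, SHS, LIS) and fixes the threshold: "ANOVA is conducted on each primary outcome, with Bonferroni-corrected α = 0.01 to control Type I error". The closing rule reads "Significance level: α = 0.05 (two-tailed) unless otherwise specified (Bonferroni-corrected α = 0.01", so the tests are two-sided. Outcomes that fail the normality check go to non-parametric tests, with Mann–Whitney U for the between-group comparison. The section also offers a joint route: "Alternative testing via MANOVA (Wilks’ Lambda, α = 0.05) proceeds to univariate ANOVAs if significant". No step-down procedure is named.

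Section 2.4 gives the design values: d = 0.50, alpha 0.05, power 0.80, and 114 participants (38 control, 76 experimental).

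**The concern.** Single-step Bonferroni holds every outcome to 0.01, however many of the others have already succeeded. Holm applies 0.01 only to the smallest p-value and relaxes the threshold after each rejection, with the same guarantee of at most a 5% chance of any false positive. When effects are expected on all five scales, as this hypothesis expects, the flat rule gives up power that could be recovered without recruiting anyone. At the planned sample size, power per outcome at 0.01 is below one half, so the loss matters to which outcomes the trial can claim.

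**Working it through.** **Inputs from the article.** Five primary outcomes (1.2, 2.7); per-outcome alpha 0.01, two-sided (2.7); d = 0.50 and 38/76 participants (2.4).

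**Inputs assumed.** The correlation between outcomes is not given, so 0, 0.3, 0.5 and 0.7 were used. The SD behind d is taken as the endpoint SD, which is equivalent to a change score with a pre–post correlation of 0.5.

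**The plan's own figure.** 0.05/5 = 0.01, exact. With independent outcomes the family-wise error is 1 − 0.99^5 = 0.049. The threshold is reproduced and valid.

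**Power per outcome at 0.01.** The expected test statistic is 0.5/√(1/76 + 1/38) = 0.5/0.1987 = 2.517. The two-sided critical value is 2.576. Power = Φ(2.517 − 2.576) = Φ(−0.059) = 47.6% (46.2% with the t distribution).

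**Holm thresholds, smallest p-value first.** 0.05/5 = 0.01; 0.05/4 = 0.0125; 0.05/3 = 0.0167; 0.05/2 = 0.025; 0.05/1 = 0.05. Testing stops at the first p-value that misses its threshold. The first step is the Bonferroni threshold and later ones are looser, so Holm cannot reject less.

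**Simulation.** 400,000 sets of five equally correlated normal test statistics, two-sided. With d = 0.5 on all five:

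| Quantity | Rule | ρ = 0 | 0.3 | 0.5 | 0.7 |
|---|---|---|---|---|---|
| Average power per outcome | Bonferroni | 47.7% | 47.6% | 47.7% | 47.8% |
| | Holm | 57.1% | 56.9% | 56.8% | 56.5% |
| At least one significant | both | 96.1% | 88.1% | 81.6% | 73.7% |
| At least three significant | Bonferroni | 45.7% | 46.7% | 47.0% | 47.5% |
| | Holm | 58.6% | 56.2% | 55.5% | 55.0% |
| All five significant | Bonferroni | 2.4% | 9.1% | 14.9% | 22.4% |
| | Holm | 14.9% | 26.8% | 34.4% | 42.6% |
| | each at 0.05, unadjusted | 18.3% | 30.4% | 38.0% | 46.7% |

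**Family-wise error with no effect anywhere.** 4.9%, 4.6%, 4.2% and 3.5% across the four correlations, the same for both rules. With effects on only some outcomes, Holm uses more of the allowance but stays within it: with three true effects, 3.1–3.2% against 1.8–2.0% for Bonferroni.

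**Less favourable effect patterns.** With d = 0.5 on three outcomes and none on two, average power over those three rises from about 47.7% to about 51%. With an effect on one outcome only, the gain is 0.2 points or less. Two affected outcomes were not simulated; the gain should lie between these. With d = 0.5, 0.4, 0.3, 0.2 and 0.5, average power rises from about 29% to 32–34%.

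**The case against.** The strongest reply is that nothing here is an error. Bonferroni at 0.05/5 is exact, matches the five scales and controls family-wise error strongly, so a claim may already be made for each outcome that passes. It also gives simple matching confidence intervals, and section 2.7 commits to reporting intervals. All of that stands. The point is about efficiency. It is still open to comment although no analysis plan is shown, because the article itself fixes the 0.01.

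The size of the gain is also conditional. An effect of 0.5 on all five outcomes favours Holm. The gain is nil for at least one success and small when few outcomes respond. The rise for all five should not be the headline: if all five were required, no adjustment would be needed, and plain 0.05 tests do better (38.0% against 34.4% at correlation 0.5).

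A reader might go further and infer that 0.01 is the wrong correction for a joint hypothesis, or that the same data could confirm or refute the trial's claim because no number of successes is set. The article does not support that. The joint reading rests largely on one word, *across*, in section 1.2; section 4 goes measure by measure, and section 2.7 tests outcome by outcome. The sentence in section 6 that integration "produces superior psychological and embodied outcomes compared to traditional dance instruction alone" is narrative, in a paragraph that opens by making the approach conditional on future data. A non-significant outcome fails to support a hypothesis; it does not refute it. How to summarise a mixed result is a gap of interpretation, and Holm does not close it.

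The MANOVA route does not answer the point either: section 2.7 does not say when it replaces the separate ANOVAs, and gives no specific alpha for its follow-up tests.

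**Conclusion.** The point holds as a missed efficiency. The flat 0.01 is valid but dominated: Holm has the same 0.05 bound and never rejects less. At the planned 76 vs 38, with d = 0.5 on all five outcomes and correlations of 0 to 0.7, it adds about 9 points of average power per outcome (about 48% to about 57%) and 7.5 to 13 points to the chance of at least three successes (45.7–47.5% to 55.0–58.6%). The figures rest on the assumed correlations, the common effect and the SD convention stated above; the dominance does not. Holm does not bring power per outcome to the planned 80%. That shortfall arises largely because section 2.4 sizes the trial at alpha 0.05 while section 2.7 tests at 0.01, which is a separate matter.

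**What to change.** In section 2.7, replace the flat 0.01 with Holm's procedure over the five primary between-group p-values: order them, compare with 0.01, 0.0125, 0.0167, 0.025 and 0.05 in turn, and stop at the first failure. Define the family as one between-group p-value per outcome, from whichever test section 2.7 assigns to it, parametric or non-parametric, so that an outcome sent to Mann–Whitney stays in the family. State that claims are made outcome by outcome. As a minor wording point, describe superiority *across* the outcomes only if all five succeed; otherwise name those that did.

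The cost is a few sentences, fixed before outcomes are compared by group, with no extra data or participants. The real downside is that confidence intervals matched to Holm are less simple than Bonferroni intervals, so the text should say which intervals will be reported.
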